### Safety evaluation

According to the World Health Organization definition, adverse events (AEs) refer to any untoward medical occurrences during interventional treatment, regardless of their causal relationship with the intervention (65). Potential adverse events related to acupuncture included dizziness, nausea, bleeding, subcutaneous hematoma, severe pain, pruritus at needling sites, needle sticking, and needle breakage. Withdrawal-related reactions during NBZDs dose reduction included anxiety, rebound insomnia, headache, palpitations, and excessive sweating. AE severity was graded as mild, moderate, or severe (66); causality was classified as definite, probable, possible, unrelated, or undeterminable. All AEs were documented in the case report form (CRF).

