## Methods

### Study design

This study is a single-center, randomized, controlled, single-blind clinical trial conducted at the Department of Acupuncture and Moxibustion, Zhejiang Provincial Hospital of Traditional Chinese Medicine. The trial period is scheduled from September 2025 to December 2026. Eligible participants will be randomly assigned in a 1:1 ratio to either the electroacupuncture group or the sham electroacupuncture group using a centralized randomization system.

A total of 78 participants will be enrolled, with 39 participants allocated to each group. Each participant will undergo three study phases: a screening period, a 6-week treatment period, and a follow-up period, with an overall study duration of approximately 12–13 weeks (Figure 1). The study protocol has been approved by the Ethics Committee of Zhejiang Provincial Hospital of Traditional Chinese Medicine (Approval No.: 2025-KLS-532-01) and will be conducted in accordance with the Consolidated Standards of Reporting Trials (CONSORT) guidelines and the Standards for Reporting Interventions in Clinical Trials of Acupuncture (STRICTA). The study flowchart and procedure are depicted in Figure 1 and Table 1.

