### NBZDs tapering protocol

Based on the 2025 European clinical practice guideline recommending a gradual dose reduction of 10–25% per week for NBZDs (27), and supported by two clinical studies that successfully employed a weekly 25% reduction strategy (21, 28), NBZDs will be reduced at a rate of 25% of the baseline dose per week. If participants experience intolerable withdrawal symptoms during tapering—such as exacerbation of insomnia, anxiety, or agitation—the dose will be temporarily reverted to the previous level. Tapering will be reattempted during the subsequent evaluation cycle (1 week per cycle).

Throughout the treatment period, participants will attend weekly in-person consultations and receive twice-weekly telephone follow-ups. Dose adjustments will be conducted through a shared decision-making process, enabling participants to actively engage in symptom monitoring and self-management under physician supervision. Final dosage modifications will require investigator approval.

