### Outcome measures

#### Primary outcome measures

The successful discontinuation rate at the end of the 6-week treatment was defined as the proportion of patients who had completely ceased NBZDs use (any dose) during the final week of treatment (days 36–42). Medication adherence was verified using patients’ daily diaries and medication records. Patients completed a daily diary card, on which they recorded the date, medication name, dose, time of administration, and any adverse reactions. The diary cards were returned to the physician at each weekly visit, and prescription records were cross-checked by an independent observer every 3 weeks. Any discrepancy between the diary and medication records will be resolved by consensus of two blinded independent investigators based on all available data (daily diaries, medication records). Urine or blood drug concentration testing was not performed to confirm participants’ self-report of hypnotic discontinuation, due to the short half-life of NBZDs (requiring daily sampling, which is logistically infeasible) and the increased participant burden that would likely raise dropout rates. The multi-source adjudication approach described above was considered a reliable alternative.

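### Adverse events are defined only for the treatment period, so a withdrawal reaction that begins in weeks 7–10 is not graded or reported as one

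*Protocol article*

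**What the plan says.** The protocol article's Safety evaluation section states that "adverse events (AEs) refer to any untoward medical occurrences during interventional treatment, regardless of their causal relationship with the intervention". It then lists the expected withdrawal reactions: "Withdrawal-related reactions during NBZDs dose reduction included anxiety, rebound insomnia, headache, palpitations, and excessive sweating". AEs are given a severity grade and a causality class and are entered in the case report form (CRF).

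The Study design section divides each participant's time into "a screening period, a 6-week treatment period, and a follow-up period". Table 1 shows treatment in weeks 1–6 and follow-up in weeks 7–10.

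The tapering section says that "NBZDs will be reduced at a rate of 25% of the baseline dose per week". If withdrawal symptoms become intolerable, "the dose will be temporarily reverted to the previous level", and the reduction is tried again in the next one-week cycle. No limit on the number of reversions is stated.

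The primary outcome is no use of a non-benzodiazepine hypnotic (NBZD) on days 36–42.

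Two instruments continue after week 6. The medication diary is scheduled for every week to week 10, and its card has a field for adverse reactions. The BHWSS is scheduled at weeks 2, 4, 6, 8 and 10; it is a secondary outcome, and the Efficacy evaluation criteria place it among the medication reduction responses.

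**The concern.** Stopping the drug is what this trial sets out to achieve, so reactions to stopping are its central safety risk. They can begin after the last dose step as well as during the taper. The AE definition is tied to the interventional treatment, and the list of withdrawal reactions is tied to dose reduction. Taken as written, neither covers a drug-free participant in follow-up.

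The participants most exposed to this are those whose taper was hardest, because each reversion moves the last step closer to the end of treatment. The safety table could then understate withdrawal reactions. Safety is part of the stated objective, and the Discussion expects that a positive result would support electroacupuncture as a safe adjunct.

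**Working it through.** **Inputs from the protocol article**

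- Treatment: weeks 1–6. Follow-up: weeks 7–10 (Study design, Table 1).
- Step: 25% of the baseline dose per week (NBZDs tapering protocol).
- Reversion to the previous level, with one-week cycles (same section).
- Endpoint window: days 36–42 (Primary outcome measures).

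**Inputs that the article does not fix (assumed, shown as a range)**

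- Day of the first dose step, s: 1 or 8.
- Weeks lost per reversion, c: 1 (reverted within the cycle) or 2 (a failed week plus a week at the previous level).

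**Step 1. Reproduce the plan's own window.** Week 6 runs from day (6 − 1) × 7 + 1 = 36 to day 6 × 7 = 42, which matches the article. Follow-up runs from day 43 to day 10 × 7 = 70.

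**Step 2. Number of steps.** 100% / 25% = 4 weekly steps, so the fourth step falls 3 × 7 = 21 days after the first.

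**Step 3. First day at zero dose after r reversions.** D = s + 21 + 7 × c × r.

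| s | c | r = 0 | r = 1 | r = 2 | r = 3 |
|---|---|---|---|---|---|
| 1 | 1 | 22 | 29 | 36 | 43 |
| 1 | 2 | 22 | 36 | 50 | 64 |
| 8 | 1 | 29 | 36 | 43 | 50 |
| 8 | 2 | 29 | 43 | 57 | 71 |

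Day 36 is therefore reached after one reversion in two of the four readings and after two in a third. In the fourth, a single reversion passes over it to day 43.

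**Step 4. Drug-free days inside the AE window.** If the window closes on day 42, this is 43 − D. If it closes on day 70, it is 71 − D.

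- D = 22: 21 days, against 49.
- D = 29: 14 days, against 42.
- D = 36: 7 days, against 35.

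A participant at zero dose from day 36 has no use on days 36–42 and so counts as a success.

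**Step 5. Does anything else carry AEs past day 42?**

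- Diary: it runs to week 10 and can record a reaction, but the definition does not make a later entry an AE. Cards are returned at weekly visits, and the weekly visits and twice-weekly calls are described only for the treatment period.
- BHWSS at weeks 8 and 10: a self-report score, with no AE severity grade or causality class.
- Table 1: the adverse events line has no week marked and may be a heading. The row beneath it, marked for weeks 0–10, concerns reasons for dropout or withdrawal.

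None of these extends the definition.

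**The case against.** The best reply is that the sentence paraphrases a general WHO definition and sets no cut-off: Safety evaluation never mentions day 42. A condensed article may leave the collection period to the full protocol and the CRF. The list of withdrawal reactions gives examples and is not an onset rule. Follow-up symptoms are also seen, through the diary and the BHWSS, and withdrawal symptoms will be analysed over time.

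Much of this stands. The symptoms are not lost from view, and a fuller document may settle the window. But the article does more than stay silent. It gives a definition tied to treatment, and elsewhere it separates treatment from follow-up. A BHWSS score is not a graded AE and need not reach the safety table.

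A reader might infer three stronger things that the article does not support.

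- **That AE collection closes for most participants around their last dose change.** The planning rates of 50% and 10.83% imply 39 × 0.50 + 39 × 0.8917 = 54.3 of 78 not meeting the endpoint. That figure can include participants held at a stable dose or withdrawn, and it does not date anyone's last step.
- **That tapers run past day 42.** The abstract describes tapering over 6 weeks, and no section provides for later steps. Entries of day 43 or more in the table are only arithmetically possible.
- **That the comparison of AEs between arms is biased in a known direction.** If one arm tapers faster, the arms reach day 42 at different stages, so bias is possible. Its direction and size are unknown, and the article has no data on when reactions begin after the last step.

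**Conclusion.** The point holds as a gap in classification, grading and reporting. On the literal text, a withdrawal reaction with onset on days 43–70 is not an AE, although the trial is still in contact with the participant and may record the symptom.

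The size is best given as observation time. A counted success can have as few as 7 drug-free days in the AE window, and extending the window to week 10 adds 28 days (35 − 7). This is not the default course: without reversions there are 14 or 21 such days. The result rests on the assumed first step day and weeks lost per reversion, and on reading the interventional treatment as the 6-week treatment period. How many participants would be affected cannot be estimated from the article. This is a cheap improvement to the safety reporting and does not threaten the primary analysis.

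**What to change.** In Safety evaluation:

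- Define the AE window as the first treatment session to week 10.
- Describe withdrawal reactions as those with onset during or after dose reduction.
- Follow AEs still present at week 6 to resolution or week 10, using the existing diary and the week 8 and week 10 assessments. State how diary cards are collected once the weekly visits end.
- Tabulate AEs by arm separately for weeks 1–6 and weeks 7–10.
- Mark the same weeks against adverse events in Table 1.

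The cost is a wording change, some extra CRF work and a somewhat larger reported AE count. No assessment point is added, and no dose or clinical rule changes.

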### Sample size

The expected discontinuation efficacy rate for the sham acupuncture group in the sample size calculation was derived from a randomized controlled trial that enrolled 144 long-term benzodiazepine users (21). However, this trial yielded a negative result, which might be attributable to the simultaneous inclusion of both BZDs and NBZDs in the study medication (22). Therefore, only the sham acupuncture group discontinuation rate of 10.83% was adopted from that trial, while the expected successful discontinuation rate for the acupuncture group was based on our pilot study.

A pilot study was conducted at our center prior to the main trial to assess the feasibility of the intervention and to obtain preliminary estimates of effect size. Ten eligible patients with chronic insomnia disorder who had used NBZDs regularly for >6 months received electroacupuncture (three times per week for 6 weeks) combined with the standardized 6-week NBZD tapering protocol (25% dose reduction every week). The successful discontinuation rate was 50.00% (5/10). No serious adverse events were reported. Detailed pilot study results are provided in Supplementary Appendix S2.

Based on expected outcomes and relevant published literature (21), this study hypothesized that after treatment, the discontinuation efficacy rates of NBZDs at 6-week post-treatment for the electroacupuncture group and sham needle and sham electroacupuncture group would be 50.00 and 10.83%, respectively. This study set *α* = 0.05 and 1-*β* = 0.90, employing a two-sided test with equal sample sizes between treatment and control groups. Referencing the sample size estimation formula for comparing efficacy rates between two groups from Sun Zhenqiu’s Medical Statistics, the calculation formula was as follows:

$$n=1641.4/{\left[\frac{\left(u_{\alpha }+u_{\beta }\right)}{\sin^{-1}\sqrt{P_{1}}-\sin^{-1}\sqrt{P_{2}}}\right]}^{2}$$

where 
$u_{\alpha }$
=1.96 (for 
α
=0.05, two-sided), 
$u_{\beta }$
=1.282 (for 
β
=0.10), P_1_ = 50.00%, and P_2_ = 10.83%. The calculation yields n = 31.7 ≈ 32 cases. Accounting for dropout rates, the clinically set dropout rate is 20%, resulting in a final sample size of 39 participants per group, totaling 78 participants across both groups.

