Various strategies have been explored to facilitate safe and effective BZRAs discontinuation. Pharmacological substitution approaches, although commonly employed, may provoke adverse effects such as panic symptoms (12), increase fall risk (13, 14), or anticholinergic side effects including dry mouth and dysgeusia (15). Moreover, individualized and standardized protocols for BZRAs dose conversion and tapering remain inadequately established (16). In the absence of medications specifically approved by the U.S. Food and Drug Administration or the China National Medical Products Administration for BZRAs dependence or withdrawal, non-pharmacological approaches have attracted increasing attention. Acupuncture has been incorporated into the most recent Chinese clinical guidelines for the diagnosis and treatment of insomnia as a recommended therapeutic option (17, 18). As a widely utilized complementary therapy for insomnia, acupuncture has demonstrated efficacy in improving total sleep time, sleep efficiency, and both subjective and objective sleep quality, while also alleviating cognitive impairment and mood disturbances, with a favorable safety profile (19, 20).

More recently, interest has emerged in the potential role of acupuncture as an adjunctive intervention during BZRAs tapering. A randomized controlled trial by Yeung et al. found no significant difference between electroacupuncture and sham acupuncture in discontinuation rates or withdrawal symptom severity during a four-week tapering protocol (21). Subsequent methodological analyses suggested that the inclusion of both BZDs and NBZDs within the same cohort may have confounded the findings, as different BZRAs subtypes are associated with distinct pharmacokinetic profiles and withdrawal trajectories (22).

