NBZDs, such as zolpidem, zopiclone, and zaleplon, are currently recommended as first-line pharmacological treatments for insomnia in many clinical guidelines owing to their shorter elimination half-lives, lower residual sedation, and comparatively reduced dependence potential relative to traditional BZDs (23). Accordingly, NBZDs have become the most commonly prescribed hypnotics in China. Notably, a recent clinical trial reported that electroacupuncture significantly alleviated withdrawal symptoms, improved sleep architecture, increased deep sleep duration, and reduced medication dependence in patients with chronic insomnia undergoing zolpidem tapering (24). The divergent findings of existing studies suggest that acupuncture may exert differential effects during NBZDs discontinuation specifically, rather than across all BZRAs subtypes.

Taken together, current evidence regarding acupuncture as an adjunctive therapy for hypnotic tapering remains limited and inconsistent, particularly with respect to NBZDs. Therefore, this single-blind, randomized, sham-controlled trial is designed to evaluate the efficacy and safety of electroacupuncture as an adjunctive intervention for NBZDs tapering in patients with chronic insomnia disorder. By systematically assessing medication discontinuation rates, sleep quality, daytime functioning, and withdrawal-related outcomes, this study aims to provide robust evidence to inform clinical decision-making in the management of long-term hypnotic use.

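### The sample-size formula as printed is inverted, and its correct form gives 26 per group rather than 31.7; the 20% dropout step should give 40 rather than 39; and the 90% power holds only for one cross-study pair of rates

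*Protocol article*

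**What the plan says.** The Sample size section sets a two-sided α of 0.05, 90% power and equal groups. The electroacupuncture rate, 50.00%, comes from a pilot of ten patients at the same centre, all treated, of whom five stopped. The control rate comes from an earlier sham-controlled trial: "only the sham acupuncture group discontinuation rate of 10.83% was adopted from that trial". The section suggests that this trial's negative result may be due to enrolling users of both benzodiazepines and non-benzodiazepines. The Introduction adds that its comparison was made "during a four-week tapering protocol".

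The formula is taken from a medical statistics textbook and printed as 1641.4 divided by the square of (u_α + u_β) over the difference of two arcsine-transformed proportions. The section then states "The calculation yields n = 31.7 ≈ 32 cases" and, after a 20% dropout allowance, "resulting in a final sample size of 39 participants per group, totaling 78 participants across both groups".

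Under Potential impact and clinical implications, the article says that a null result would be important negative evidence. Study limitations acknowledges that the small pilot makes the effect size uncertain.

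**The concern.** A reader who puts the stated inputs into the stated formula should obtain the stated n. Here the printed expression is upside down, its usual form gives a different number, and the dropout inflation uses the wrong operation. The chain from assumptions to 78 participants therefore cannot be checked from the text.

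The 90% power also depends on the difference between two rates from different studies, and only one of those studies had a control arm. If either rate is off, power can fall well below 90%, and a null result would then say less than the Discussion expects of it.

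**Working it through.** **Inputs (Sample size section).** P₁ = 0.50, P₂ = 0.1083, u_α = 1.96, u_β = 1.282 (sum 3.242), constant 1641.4, dropout 20%.

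**1. Trying to reproduce 31.7**

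- Arcsines in degrees: asin√0.50 = 45.00 and asin√0.1083 = 19.21; difference 25.786. In radians the difference is 0.45006.
- Formula as printed, degrees: (3.242/25.786)² = 0.015807, and 1641.4/0.015807 ≈ 103,842.
- Formula as printed, radians: (3.242/0.45006)² = 51.89, and 1641.4/51.89 = 31.63.
- Standard form, degrees: 1641.4 × 0.015807 = 25.95, so **26 per group**. The radian equivalent, 0.5 × 51.89 = 25.95, agrees, which confirms that 1641.4 is the degree-scale constant and should multiply.
- Two-proportion formula, pooled variance: mean rate 0.30415, n = 26.86. With continuity correction, n/4 × [1 + √(1 + 4/(n × 0.3917))]² = 31.76.

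Two routes come close to 31.7: the inverted formula in radians (31.63) and a continuity-corrected method that the document never mentions (31.76, or 31.75 with unrounded normal quantiles). The text does not show which was used, if either.

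The inverted form is not a valid sample-size formula. In radians, with sham held at 10.83%, it gives 31.6 for an electroacupuncture rate of 50%, 19.1 for 40% and 9.3 for 30%, so smaller effects appear to need fewer patients. The standard form gives 26, 43 and 88 (25.95, 43.05 and 88.05 before rounding).

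**2. Dropout**

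- From 32: 32/(1 − 0.20) = 40 per group, 80 in total.
- The plan's 39 matches 32 × 1.2 = 38.4, rounded up.
- 39 × 0.80 = 31.2, so about 31 per group remain.
- From 26: 26/0.80 = 32.5, so 33 per group, 66 in total.

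**3. Power at the stated rates** (50% against 10.83%, exact binomial enumeration, two-sided 5%)

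| Analysed per arm | Fisher | Chi-square |
|---|---|---|
| 26 | 83% | 91% |
| 31 | 91% | 94.5% |
| 32 | 92% | 95% |
| 39 | 96% | 98% |

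**4. Power at other rates, 31 per arm.** Every rate other than 50% and 10.83% is an assumption used to show the range.

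| Electroacupuncture | Sham | Fisher | Chi-square |
|---|---|---|---|
| 50% | 15% | 80% | 86% |
| 50% | 20% | 62% | 71% |
| 50% | 25% | 44% | 54% |
| 50% | 30% | 28% | 37% |
| 40% | 10.83% | 69% | 78% |
| 30% | 10.83% | 35% | 47% |

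With all 39 per arm analysed, 50% against 20% gives 73% (Fisher) or 81% (chi-square). The exact (Clopper–Pearson) 95% interval for the pilot's 5/10 is 18.7% to 81.3%.

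**The case against.** The strongest reply is that nothing is lost. The formula slip errs on the safe side (39 planned, against 33 from the correct arcsine form with dropout), the dropout slip is one patient per group, and power stays above 90% at the stated rates. This stands, and it limits the severity.

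Several stronger readings are tempting but not supported:

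- *That 32 is a wrong number.* It is a defensible size for these inputs under a continuity-corrected formula. The fault is the mismatch between method and result. Nor may one assume that the continuity-corrected method was the one used, since the printed division in radians also comes close.
- *That the document regards the earlier trial's population as non-comparable.* It says only that the drug mix might explain the negative result and may have confounded it. The fair remark is that it uses the mix to discount that result and still keeps the sham rate.
- *That the sham rate here must exceed 10.83%.* The Introduction credits non-benzodiazepines with "comparatively reduced dependence potential relative to traditional BZDs", and the treatment period here is six weeks, which could point upward. But the inclusion criteria require a failed attempt to stop, the primary outcome requires no use at all in the final week, and the tapering section cites the same trial for its weekly reduction. The direction is open.

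Study limitations does admit the pilot's imprecision, calls the study exploratory and plans to pool pilot and main-trial data. That is a partial answer: it does not address the sham rate, and a single-arm pilot adds no control data. It is also fair that some dropouts may stay in the full analysis set, so 31 per arm is the cautious case.

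**Conclusion.** The point holds, at moderate severity. With the stated inputs, the arcsine formula correctly oriented gives 26 per group, not 31.7, and 32 evaluable patients with 20% dropout require 40 randomised, not 39. How 31.7 arose cannot be settled from the document. These errors do not bring power below 90% at 50% against 10.83%.

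Separately, the 90% is conditional on both rates. At 31 per arm, moving sham to an assumed 20% lowers power to 62% (Fisher) or 71% (chi-square), and moving electroacupuncture to an assumed 40% lowers it to 69% or 78%. A reader might infer that the trial is underpowered. The documents do not show that, because they do not establish what the true rates are. They show only that the single stated figure conveys more certainty than its sources allow.

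**What to change.** Revise the text of the Sample size section:

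1. Print the arcsine formula as a multiplication and give its result as 26 per group, or have the sponsor state the method that actually produced 32. Correcting to 26 is no reason to reduce enrolment, since 26 analysed per arm has only 83% power by Fisher's test.
2. State that 39 randomised per group leaves about 31 after 20% dropout, with about 91% (Fisher) or 94.5% (chi-square) power at the stated rates, or that 32 evaluable would require 40.
3. Make the 90% conditional by adding a short table of power over assumed sham and electroacupuncture rates, such as the one above, and note the pilot's 19% to 81% interval.
4. Under Potential impact and clinical implications, tie the negative-evidence statement to that table.

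No additional patients are needed. The cost is that the stated power becomes conditional and looks less favourable.
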